### Sample size estimation

A total of 32 subjects (16 for the experimental group and 16 for the control group) should be recruited to obtain a 1:1 ratio, 80% power (beta error = 20%) and 95% safety (alpha error = 5%), and assuming according to the results evidenced by Nguyen et al. [28] that intervention in the experimental group will cause a 3% increase, with ± 6 standard deviation, in the identification of dyspnea self-management. A final sample size of 44 subjects (22 for the experimental group and 22 for the control group) has been determined to minimize the effects of potential losses in statistical power.

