
## Methods/design

### Study design

A randomized, controlled, single-blind, two-arm parallel clinical trial will be conducted during six months to assess the efficacy of a mobile application in the follow-up of patients on home oxygen therapy. The control group will include patients on oxygen therapy subject to conventional follow-up methods (regular visits of a respiratory therapist), while the intervention group will include patients followed through conventional methods and through the use of the mobile app “AppO_2_” (Fig. 1).

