#### Statistical analysis

A descriptive analysis of the study variables will be performed, characterizing patients, generating graphs and frequency tables for qualitative variables, and estimating measures of central tendency (mean), dispersion (standard deviation) and position (distribution limits and range) for quantitative variables.

For bivariate analysis, a Student’s t test will be conducted to compare two means, whereas a chi-squared test and Fisher’s exact test will be used for qualitative variables. For analyzing three mean values or more, a repeated measures analysis of variance (ANOVA) will be used. Multiple lineal regression models will be applied to adjust the impact of the use of the app and to remove the effect of confusing factors, estimating standardized beta coefficients, an adjusted determination coefficient, and residual values. An alpha error of < 5% will be accepted and 95% confidence intervals (95% CI) will be estimated for all statistical analysis, and the SPSS Statistics software, 25.0 version (IBM Corp) will be used.

**Formal committee**: no need for a formal committee as the trial is short with minimal known risks.

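### The sample-size figures contradict one another: for a difference of 3 with SD 6, 16 per arm gives about 28% power, not 80%

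*Protocol article*

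**What the plan says.** The Study design section sets out a parallel comparison of two groups: "A randomized, controlled, single-blind, two-arm parallel clinical trial will be conducted during six months".

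The Sample size estimation section states that "A total of 32 subjects (16 for the experimental group and 16 for the control group) should be recruited to obtain a 1:1 ratio", with 80% power and a 5% alpha error. The assumption, taken from a cited study, is that "intervention in the experimental group will cause a 3% increase, with ± 6 standard deviation, in the identification of dyspnea self-management". The number is then raised to allow for losses: "A final sample size of 44 subjects (22 for the experimental group and 22 for the control group"). That section gives no formula, sidedness, loss rate or baseline correlation.

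The Statistical analysis section says that "a Student’s t test will be conducted to compare two means". It also lists repeated measures ANOVA for three or more means and multiple linear regression for adjustment, and plans 95% confidence intervals throughout. It does not say which method is used for the primary outcome. The registration table in the article lists recognition of dyspnea self-management as that outcome.

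**The concern.** A difference of 3 with SD 6 is a standardised effect of 0.5. Detecting an effect of that size between two independent groups takes far more than 16 per arm, so the section looked inconsistent on its face.

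The power statement governs how the result will be read. A reader told that the trial has 80% power will take a non-significant comparison as fair evidence that the app does not work. If the assumed effect is real and the printed inputs are right, a t test would miss it in about 72% of repetitions with 32 analysed (100 − 28) and about 63% with 44 analysed (100 − 37).

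**Working it through.** **Inputs from the article:** two parallel arms, 1:1; 16 per arm, raised to 22; difference 3; SD 6; alpha 5%; power 80%.

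**Assumptions that the article does not state:**
- The effect is printed as a percentage and the SD without a unit. I take both on the same scale, so d = 3/6 = 0.5.
- The test is two-sided, in line with the planned 95% intervals. One-sided results are given as well.
- The two-sample t test is the benchmark.

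**Step 1: try to reproduce 16 per arm.** The two-sample normal formula is n per arm = 2 × (1.96 + 0.8416)² / d².
- (1.96 + 0.8416)² = 7.849.
- n = 2 × 7.849 / 0.25 = 62.8, so 63 per arm (126 in total).
- The exact noncentral t calculation gives 64 per arm (128 in total).
- One-sided: 50 per arm (normal) or 51 (t).

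The stated figure is not reproduced. It is a quarter of what the inputs require two-sided (16/64).

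**Step 2: power at the stated sizes.** By the normal approximation, power ≈ Φ(d × √(n/2) − 1.96).
- n = 16: 0.5 × √8 = 1.414, and Φ(−0.546) = 29.3%.
- n = 22: 0.5 × √11 = 1.658, and Φ(−0.302) = 38.2%.

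| Per arm | Two-sided, normal | Two-sided, t | One-sided, t | Difference detectable with 80% power (two-sided t, SD 6) |
|---|---|---|---|---|
| 16 | 29.3% | 27.8% | 39.6% | 1.024 × 6 = 6.1 |
| 22 (no losses) | 38.2% | 36.7% | 49.5% | 0.865 × 6 = 5.2 |

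The detectable differences are about twice the assumed 3. The expected 95% CI half-width at 22 per arm is 2.02 × 6 × √(2/22) ≈ 3.7, wider than the effect sought.

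**Step 3: what could have produced the printed number?** Two explanations fit.
- One-sample or paired normal formula with the printed inputs: 7.849 × (6/3)² = 31.4, rounded up to 32. This equals the stated total.
- Two-sample normal formula at d = 1.0: 2 × 7.849 = 15.7, rounded up to 16. This equals the stated number per arm. It would arise from a difference of 3 with SD 3, or a difference of 6 with SD 6.

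**Step 4: other readings.**
- Baseline adjustment: cutting 63 per arm to 16 needs a baseline–outcome correlation of √(1 − 16/63) ≈ 0.86. At a correlation of 0.5, 48 per arm are still needed and power at 16 per arm is 37% (normal).
- The 3% as a difference in proportions: 424 per arm for 1% against 4%, and 4,356 per arm for 50% against 53%. The attached SD also speaks against this reading.

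**The case against.** The best defence is that the number may be right and an input misprinted. With SD 3, or a difference of 6, the ordinary two-sample formula gives exactly 16 per arm. The inputs come from a cited study that is not at hand, so this cannot be excluded. It stands as a limit on the diagnosis: a power of 28% or 37% holds only if 3 and 6 are the intended figures. It does not rescue the section as printed, because an input would then be wrong.

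A reader might infer from the match with 31.4 that a one-sample number was calculated and then divided between two arms. The article does not support that as a fact: it names no formula, and the calculation at d = 1.0 fits equally well.

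It can also be said that the article does not tie the t test to the primary outcome, since adjusted regression and repeated measures ANOVA are listed too. That is fair, and the t-test figures are a benchmark rather than the power of a fixed primary analysis. But adjustment would restore 80% only with a baseline correlation of about 0.86, and none is claimed. Choosing a one-sided test still leaves 40% and 49%.

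Finally, a full protocol or analysis plan may hold more detail. That would excuse an omission, but the fault here is a stated calculation that disagrees with its own stated inputs.

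**Conclusion.** The concern holds as an inconsistency: the effect, SD, power and sample size in the Sample size estimation section cannot all be correct for a two-arm trial. On the printed inputs, 80% power needs about 64 per arm before losses, against 16 stated. Power is about 28% with 32 analysed and 37% with all 44. This rests on a common scale for 3 and 6, a two-sided 5% test and the t test as benchmark. Relaxing sidedness does not change the conclusion, and covariance adjustment would do so only at the very high correlation shown above. Which figure is wrong, and how the error arose, cannot be determined from the article.

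**What to change.** 1. Check the difference and the SD against the cited source, and state the scale of each, the sidedness and the test assumed. If either was misreported, correct it and show that 16 per arm then follows.
2. If 3 and SD 6 are as intended, keep 44 and replace the 80% claim. Suggested wording: *With 22 per arm, a two-sided 5% two-sample t test has 37% power for a difference of 3 with SD 6 (28% if only 32 participants complete). Power of 80% is reached for a difference of about 5.2 (about 6.1 with 32 completers). The result will be reported as the effect with its 95% confidence interval, and a non-significant test will not be taken as evidence of no effect.*
3. If the authors prefer to keep 80% power for 3 with SD 6, the number to state is 64 per arm before losses.

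The second route needs no extra patients. Its cost is a less favourable stated power and matching changes wherever the article promises an assessment of efficacy, notably the Abstract, the end of the Background, the Study design section and the Discussion.

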**Fig. 2 Fig2:**
[figure not shown]
Participant Timeline

#### Eligibility criteria (inclusion and exclusion criteria)

To obtain a homogeneous study population, the following eligibility criteria have been established:

Inclusion criteria.Subjects of 18 years and older.Subjects with PaO_2_ < 60 mmhg, SO_2_ < 89% and dyspnea. Patients on home oxygen therapy enrolled in a home healthcare program during the study period.Subjects whose disease has progressed for 1 year or more.Subjects accepting to participate in the study by providing informed consent.

Exclusion criteria.

The following subjects will be excluded from the study:Subjects with invasive and/or non-invasive mechanical ventilation.Subjects incapable of using the mobile app or subjects without a smartphone with an operating system (Android or iOS) and available mobile data connection.

### Study variables

The following outcome variables and independent variables are suggested to reach the study purpose:

### Outcome variables

Oxygen saturation, measured by a pulse oximeter, as well as capillary refill, respiratory rate, heart rate, and duration of the oxygen cylinder. Will be evaluated up to 6 weeks, from date of randomization until the date of first documented progression or date of death from any cause, whichever came first, assessed up to 6 months

Oxygen saturation/fraction of inspired oxygen ratio. Will be evaluated up to 6 weeks, from date of randomization until the date of first documented progression or date of death from any cause, whichever came first, assessed up to 6 months.

Saint George questionnaire for assessing health-related quality of life (HRQoL)  [30]. This questionnaire is used to measure the effects of respiratory diseases such as COPD and asthma. It comprises 50 items divided into three levels: symptoms, activity, and impact. Scores at the symptoms level describe the frequency and severity of respiratory symptoms. Scores at the activity level assess those activities that are limited by breathlessness. Scores at the impact level estimate the psychological and social changes caused by the disease, and patients answer the questions by themselves or in an interview. Its estimated duration is 10 min. Moreover, scores are individually calculated for each level and globally and range from 0 (no changes in the quality of life) to 100 points (maximal alteration). will be evaluated up to 6 weeks, from date of randomization until the date of first documented progression or date of death from any cause, whichever came first, assessed up to 6 months.

Borg dyspnea scale [31]. It is an analogue, standardized and validated scale written in Spanish, which can be applied quickly and easily to graphically assess the patients and their perception of dyspnea. It has been used since the 70 s and comprises a score ranging from 0 to 10. The scale determines the severity of the respiratory distress and has a graph close to each quantitative value, which helps patients identify their respiratory distress perception: number 10 being the highest level of dyspnea perception. Will be evaluated up to 6 weeks, from date of randomization until the date of first documented progression or date of death from any cause, whichever came first, assessed up to 6 months

Identification of dyspnea self-management and quality of life through the mobile app. Will be evaluated up to 12 weeks, from date of randomization until the date of first documented progression or date of death from any cause, whichever came first, assessed up to 6 months

- Independent variables: medical diagnosis, comorbidities, age, sex, health system affiliation regime, smoking, alcohol use, obesity, social isolation, number of people who live with the patient, caregivers required for the patient’s healthcare, prescription and compliance with oxygen therapy (hours/days), underuse of the oxygen system, level of instruction for the management of the mobile app.

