Key inclusion and exclusion criteria	Inclusion Criteria: Individuals of 18 years of age and older Patient with PaO2 < 60 mmHg, SO2 < 89% and dyspnea. Patients with home oxygen therapy enrolled in-home care programs during the study period. Time of evolution of the disease greater to one year Patients who express their willingness to participate in the study through their informed consent. Exclusion Criteria: Patients with the following exceptional situations will be excluded from the study: Patients with invasive and/or non-invasive mechanical ventilation Patients with the inability to operate a mobile application or those who do not have a smartphone with an operating system (Android or iOS) and available data connection.
Study type	Interventional (Clinical Trial), Allocation: Randomized Intervention Model: Parallel Assignment Masking: Single (Participant) Primary Purpose: Supportive Care
Date of first enrolment	June 1, 2021
Target sample size	44
Recruitment status	Not yet recruiting
Primary outcome(s)	Recognition of self-management of dyspnea and through the mobile app (Time Frame: up to 12 weeks for 6 months)
Key secondary outcomes	Saint George questionnaire for the assessment of health-related quality of life (Time Frame: up to 6 weeks for 6 months)

Criteria for discontinuing or modifying allocated interventions for a given trial participant

Voluntary abandonment, death.

Participant Retention

Once a patient is enrolled or randomized, the study site will use reasonable efforts to follow the patient throughout the study period.

Interaction between users and the AppO_2_ mobile app.

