The app has a user-friendly design through which patients can intuitively access the different sections and accordingly register their data. When patients log in for the first time, they have to enter their basic data such as full name, healthcare system affiliation regime, birth date, sex, and diagnosis. Once a patient’s account has been created, the following healthcare-derived clinical results can be recorded in the “progression” section: heart and respiratory rates, SO_2_ measured with a pulse oximeter, level of dyspnea, capillary refill, and fraction of inspired oxygen. After recording a second progression, patients can see a line graph showing trends for each vital sign. Regarding the formulas included, users just have to select the fields of those elements whose values are not predetermined. This ensures that the use of formulas is not limited by a lack of information regarding certain values. In cases with limited and standardized available options (e.g., type of cylinder), there is a drop-down list such as that the desired option can be quickly selected.

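### All five listed outcomes, including the primary, are to be evaluated only until an undefined first progression or death, and each carries two time limits, so the text fixes no single primary analysis time

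*Protocol article*

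**What the plan says.** The protocol article's Outcome variables section has five entries: vital signs with oxygen cylinder duration; the saturation to inspired-oxygen ratio; the Saint George questionnaire; the Borg dyspnea scale; and dyspnea self-management, which Table 1 lists as the primary outcome.

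- **Stop rule.** All five entries run from randomisation "until the date of first documented progression or date of death from any cause, whichever came first".
- **Time limits.** The first four entries carry "Will be evaluated up to 6 weeks, from date of randomization until the date of first documented progression or date of death from any cause". The primary carries "Will be evaluated up to 12 weeks, from date of randomization". All five sentences then end with "whichever came first, assessed up to 6 months".
- **Table 1.** The primary reads "Recognition of self-management of dyspnea and through the mobile app (Time Frame: up to 12 weeks for 6 months" and the key secondary reads "Saint George questionnaire for the assessment of health-related quality of life (Time Frame: up to 6 weeks for 6 months". Neither mentions progression or death.
- **Duration.** Study design describes a "two-arm parallel clinical trial will be conducted during six months to assess the efficacy of a mobile application".
- **Retention and discontinuation.** Under Participant Retention, the site is to make reasonable efforts to follow each patient for the whole study. The discontinuation criteria list voluntary abandonment and death, and progression is not among them.
- **Other uses of the word.** In the description of the app, progression is the name of a part of the patient section. In the text on interaction with the app it is a single data entry: "After recording a second progression, patients can see a line graph showing trends for each vital sign".
- **Analysis.** Statistical analysis plans a t test for two means and repeated-measures ANOVA for three or more. It names no time point for the primary outcome.

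**The concern.** The wording suits an endpoint such as time to progression, where observation ends at the event. Here the outcomes are scores and vital signs measured repeatedly and compared as means. If measurement ends at first progression, a patient who worsens contributes nothing afterwards, and a later comparison rests on a subset selected by something that happened after randomisation. The app could change how often that event occurs, because the Discussion gives fewer exacerbations as the aim. It could also change how often the event is documented, because the app displays an alarm when vital signs leave set limits. Either route would make the remaining patients in the two arms differ for reasons other than chance.

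The second problem is the analysis time. With 12 weeks and 6 months both attached to the primary outcome and neither designated, the choice could be made after the results are known.

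**Working it through.** The protocol gives no figure for this point that could be reproduced. The main check sets the passages side by side.

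**1. Stop rule**

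| Place | What it implies for a patient who progresses |
|---|---|
| Outcome variables, all five entries | Evaluation ends |
| Study design | The trial lasts six months, with no early end stated |
| Participant Retention | Followed through the study period |
| Discontinuation criteria | Not a reason to discontinue |
| Table 1, primary and key secondary | No stop mentioned |

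The first row cannot hold together with the retention and discontinuation rows. The event that triggers it has no clinical definition anywhere in the text.

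**2. Time limits**

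| Entry | Limit in weeks | Limit in months | Table 1 |
|---|---|---|---|
| Primary | 12 weeks | 6 months | both |
| Saint George questionnaire | 6 weeks | 6 months | both |
| Other three entries | 6 weeks | 6 months | not listed |

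Taking 6 months as about 26.1 weeks, 12 / 26.1 = 46% and 6 / 26.1 = 23%. The alternative limits are therefore far apart. The saturation to inspired-oxygen ratio is also to be recorded weekly (SO2/FiO2 ratio section), a frequency that its Outcome variables entry does not mention.

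**3. False-positive rate if the time is chosen after seeing the data**

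With two two-sided tests at 5%, the chance of at least one false positive when the tests are independent is 1 - 0.95 x 0.95 = 0.0975, or 9.75%. Both tests would use the same patients, so the results would be correlated. For bivariate normal test statistics with an assumed correlation:

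| Correlation (assumed) | At least one false positive |
|---|---|
| 0 | 9.75% |
| 0.5 | 9.1% |
| 0.7 | 8.3% |
| 0.9 | 7.0% |

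**4. Can the bias be sized?**

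A simple formula for the mean difference hidden by truncation is (control progression rate - app progression rate) x drop after progression. It supposes that progressors are otherwise like the rest and that the app has no other effect. All inputs below are assumed, because the protocol gives none.

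- 40% and 25%, drop 6: 0.15 x 6 = 0.9
- 20% and 15%, drop 2: 0.05 x 2 = 0.1
- Equal rates: 0
- 25% and 40%, drop 6: -0.15 x 6 = -0.9

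The sign changes with the inputs, so neither size nor direction can be claimed.

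**5. Loss of numbers**

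This step assumes that 0% to 50% of patients progress before the analysis time and then have no value. Measured patients per arm fall from 22 to 22 x 0.5 = 11. With a difference of 3 and SD of 6 (Sample size estimation, reading its 3% increase as 3 units), power = Phi(3 / (6 x sqrt(2/n)) - 1.96):

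- n = 22: 38%
- n = 11: 22%

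That power is already low at n = 22 is a separate sample-size matter, and this point does not depend on it.

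**The case against.** The strongest reply is that the protocol, read as a whole, does not intend truncation. Study design, the retention text, the discontinuation criteria and Table 1 all point to six months of follow-up, and the progression clause looks like inherited wording. This stands in part. A reader might infer that month-6 means will come only from progression-free patients, but that is one reading of a self-contradictory text and not an established plan. The reply does not remove the clause, which is attached to every listed outcome including the primary.

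A reader might also take first progression to mean the first app upload, so that follow-up ends at once and only in the app arm. That is strained, because it would defeat the six months of reporting under Reports and the weekly recording. The second meaning shows only that the word is ambiguous.

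The time limits may be awkward English for every 6 or 12 weeks over 6 months. That is plausible and would settle the measurement schedule, but it would leave two candidate times for the primary. Repeated-measures ANOVA could take several times in one model, but the text does not say that the primary outcome will be tested that way, and no passage plans to pick a time after the fact. Visit times may stand in Figure 2, which is not shown, so the finding is limited to the visible text.

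Finally, it would be too strong to say that every outcome carries all three limits. Each entry carries two. Exacerbations and oxygen underuse, named as outcomes in the Abstract, have no limit in this section.

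**Conclusion.** The point holds as an error in stated text, not as missing detail. The stop at progression or death is written into all five listed outcomes, rests on an undefined event, contradicts the retention and discontinuation text, and does not suit the planned comparison of means. If applied, it would remove values after a post-randomisation event that the app could affect, and the randomised comparison would be lost. The size and direction of that bias cannot be stated, because no progression rate is given.

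Separately, the visible text fixes no single analysis time for the primary outcome, even on the benign reading of the time limits. If the time were chosen after seeing the data, the false-positive rate would exceed 5%, with 9.75% as the ceiling under independence and about 7% to 8% at assumed correlations of 0.9 to 0.7.

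**What to change.** - Delete the stop at progression or death from all five entries under Outcome variables. State that outcomes are collected to 6 months in every randomised patient who is alive, whether or not progression has occurred, and report deaths separately by arm.
- Reword the time limits as a measurement schedule, and reconcile it with the weekly recording of the saturation to inspired-oxygen ratio.
- Name one primary analysis time in advance, with the other as secondary. Six months matches the length of the intervention. Twelve weeks would also solve the problem if the sponsor justifies it.
- Bring Table 1 into line with the revised text.

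The cost is wording, plus some assessments after progression that fall within the six months of follow-up already planned. The protocol gives no visit frequency, so the number of extra assessments cannot be stated.
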